## Abstract

Background: Chronic nonspecific neck pain is the most frequent form of neck pain. It is more prevalent in women, and a costly public health issue. It is commonly associated with biomechanical, functional, proprioceptive, and postural impairments. The aim of this trial is to compare the effects of global postural exercises versus specific therapeutic exercises on neck pain, disability, mobility, pressure pain threshold, kinesiophobia, pain catastrophizing, postural control, and neuromuscular efficiency in women with chronic nonspecific neck pain. Methods and analysis: This study is a randomized, parallel-group and single blinded clinical trial. Sixty-two women with nonspecific chronic neck pain were recruited from the community of Guarda, Portugal, and randomly assigned to one of two intervention groups: (1) global postural reeducation (GPR group), (2) specific therapeutic exercises (STE group). The intervention was carried out over 4 weeks, with two sessions per week (eight sessions), and applied by a physiotherapist and paired with a daily individual at-home-exercise program. Primary outcomes are neck pain intensity and disability (Numerical Pain Rating Scale, Neck Disability Index). Secondary outcomes are cervical mobility and pressure pain threshold (CROM, algometry), attitude to pain (kinesiophobia, pain catastrophizing), standing postural control (Center of Pressure (COP) displacements), and neuromuscular efficiency (electromyography). There are four points of evaluation where the outcomes were assessed twice before the intervention, 1 week apart, and the two post-intervention assessments will be carried out after four and eight sessions. The objective was to increase scientific knowledge of different exercise modalities, such as global postural reeducation, in musculoskeletal disorders. Trial registration: ClínicalTrials.gov (NCT04402463), prospectively registered (data 22 May 2020).

## 1. Introduction

Nonspecific neck pain is an increasingly frequent musculoskeletal condition [1,2,3] affecting 22% to 70% of the population [4,5] that is more prevalent in women than in men [6]. Some patients will not experience complete resolution of pain and disability, which can become a more complex chronic pain syndrome [7]. When symptoms persist for more than 12 weeks, the condition acquires the value of chronicity and is denominated chronic nonspecific neck pain (CNSNP) [8]. This is associated with high costs for public health [9], and is becoming a socio-health problem [3].

The mechanisms underlying recurrence or persistence of neck pain may be associated with biomechanical, functional, proprioceptive, and postural changes [10,11,12,13,14,15]. However, the multidimensional nature of CNSNP can involve not only the sensory–motor component, but also psychosocial components, such as anxiety, depression, and fear and catastrophic thoughts in response to pain (kinesiophobia and pain catastrophizing) [4,16,17,18].

In postural control, the accurate functioning of the proprioceptive neck system is especially important in order to keep the joint position sense (JPS) and the movement control of the head and cervical spine intact [19]. Considering that neck muscles have a very high density of muscle spindles, especially in the suboccipital region [20], and that the cervical sensory afferences have strong influences on vestibular and visual systems to control postural stability [21,22], impaired neuromuscular function of the neck muscles can greatly influence postural control deficits [23].

Many studies have shown that people with cervical pain have abnormal contraction patterns of superficial and deep cervical flexor muscles [24,25,26,27,28], abnormal strength/endurance of deep cervical flexors (DCF) [29,30,31,32], impaired control and velocity of movement [33], proprioceptive and kinesthesic deficits [15,34,35,36,37], impaired postural control [13,15,22,23,38,39], decreased range of motion [3,15,40,41], low threshold for pressure pain, and general sensitization of the central nervous system [3,42,43,44,45].

Several non-pharmacologic treatments, such as manual therapy and therapeutic exercise, minimize neck pain and disability [46,47,48,49]. There are also other resources, such as pain neuroscience education, dry needling, shock waves, etc., that have shown beneficial effects on pain and disability [50,51,52,53]. It is always difficult to consider treatments with a single technique, and in this sense, some studies support the combination of different types of techniques or interventions for the treatment of neck pain [48,53]. Considering the evidence surrounding the variety of techniques in the treatment of neck pain, we wanted to consider of the reported beneficial effects of specific therapeutic exercises (STE), normally considered as tailored low-load exercises based on sensorimotor control, on neck pain, disability, dizziness, mobility, and muscle performance [46,47,49,54]. However, we also believe that the effects of different exercise modalities aimed at neck pain should be studied in depth.

Global postural reeducation (GPR) is a conservative treatment that we can consider as a global postural exercise method, and widely used in physical therapy clinical practice in many countries [55,56]. Some studies support the clinical effectiveness of GPR in treating patients with different musculoskeletal disorders and impairments [57,58,59,60,61,62,63], including cranio–cervico–mandibular complex [64,65,66,67,68,69,70,71,72]. The main aims of GPR are to reduce postural impairments and regain muscle symmetry and adequate posture through global active muscular stretching postures and joint decompressions, with breath control, motor control, contractions of antagonist muscles, and sensory integration exercises conducted by manual contacts in order to provide proprioceptive information to the patient [61,73,74,75,76,77]. These techniques are focused on reducing pain and improving body awareness and physical conditions, such as increased mobility, flexibility, muscle strength, and functional capacity [55,56,75,78,79], to finally obtain muscle balance and postural symmetry [61,67]. These findings must be considered with caution due to the heterogeneity of the results and the low quality of the studies that reported these results [55,56,59].

GPR is based on the concept that postural muscles are organized to act in concert with each other as “muscle chains” located anterior and posterior to the spine [55,61,67,74], and it has been hypothesized that some specific clinical presentations are caused by shortened muscles or “muscle chain retractions” [61,63,67]. Treatment with an active muscle stretching method exerts physiological effects not only at spinal but also at motor cortical level, increasing the amount of intracortical inhibition and/or reducing intracortical excitation, and induces a significant reduction of motoneuron excitation, which is caused by both pre- and postsynaptic mechanisms [62]. Moreover, according to the GPR basic principles of causality, globality, and muscle chain distribution [57,61,63,66,74], all of them containing the regional interdependence model of musculoskeletal dysfunction [80], the increased cortical inhibition following GPR was not limited to a specific muscle but tended to extend to segmentally related peripheral muscles [62].

However, there are few studies following the treatment of patients with chronic nonspecific neck pain with GPR, and no study has yet compared GPR with STE in NSNP and their effects on neuromuscular patterns or efficiency using an electromyographic assessment, as well as the correlations of this with pain, disability, standing postural control, and psychosocial components [55,56].

Considering that GPR is a therapeutic intervention with an approach based on an integrated idea of the muscular, it assesses and aims to act on the role and status of the functional groups of muscles responsible for posture and its alterations that form the muscle chains [55,56,66,67,81]. Most previous studies address pain and functionality as outcome variables [55,56], and very few address specific variables of postural balance [82], muscle efficiency with EMG [70], or psychosocial factors associated with pain such as kinesiophobia [67].

Additionally, although there is little previous evidence, results from previous studies with GPR have shown effects not only on symptom improvement, such as pain and functionality [55,56], but have also had effects on patient body awareness and proprioception associated with breathing and joint decompression [68,75,76]. Thus, in our study we anticipated that GPR would improve postural stability. Even though the interventions were not specifically designed to improve balance, they both aimed to enhance neuromuscular and sensorimotor control which could potentially enhance postural stability considering its neurophysiological mechanisms [19,21,22,23,83]. Moreover, this is the first study investigating the effects of GPR on the activity of cervical flexor muscles in patients with chronic neck pain by comparing it to an exercise mode that promotes coordination between the superficial and deep cervical muscles [84]. Only one preliminary study showed that repeated active postural exercise over 2 weeks decreased sternocleidomastoid muscle activity over some progressive stages of the cranio-cervical flexion test (CCFT) [85]. This active postural exercise involved assuming a sitting lumbo-pelvic neutral postural position with the addition of an active neck-lengthening maneuver. The authors suggested that this was accompanied by an improvement in the activation of the cervical DCF [84], and they proposed future studies with active postural exercises as an alternative treatment of neck pain [85]. Moreover, the majority of clinical trials studying GPR rated the method as a low to very low-quality treatment, which means that there is substantial uncertainty in their results [55,59].

Comprehensive interventions in postural and musculoskeletal disorders could make a significant contribution to treat and prevent recurrent episodes of pain, disability, psychosocial effects, and loss of work productivity [4,55,86,87,88,89]. Thus, it is vital to know what physiological functions different therapeutic exercises, including GPR, can and cannot address.

We considered the conclusions and indications of previous studies, based on the need for high-quality prospective clinical trials comparing GPR with effective treatment strategies for neck pain, such as manual therapy or therapeutic exercises [15,55,56,59]. Taking into account what has been described above, we considered it interesting to contribute more knowledge regarding the use in clinical practice of a wider variety of methods based on exercise and manual therapy. In our study we address the GPR, which due to the heterogeneity of the results of some studies, it presents some lack of evidence that we address in our study, on parameters in the application protocols and the effects on some outcome variables not sufficiently assessed in previous studies as patterns or neuromuscular efficiency, postural control and psychosocial factors, and also compare these effects with those caused by other therapies in this study factor (CNSNP).

Therefore, this randomized parallel clinical trial will aim to evaluate the benefits of GPR and STE, as two different exercise modalities, the former more dynamic [46,47,49,54], and the latter more static/postural [61,73,77], considering that both have mechanisms of action targeting symptomatology [46,47,55,56] and muscle efficiency [46,54,68]. So, pain, disability, postural control, neuromuscular function, and the correlations between them will be assessed in women with chronic non-specific cervical pain. The primary objective is to investigate the most effective and efficient intervention to improve neck pain intensity and disability. More concretely, we will evaluate if a global postural exercise method, such as GPR, or a specific therapeutic exercise has a superior effect. The secondary objective is to assess the effectiveness of the two interventions on cervical range of motion (CROM), pressure pain threshold (PPT) in the cervical region, kinesiophobia, pain catastrophizing, standing postural control, and neuromuscular efficiency of superficial cervical flexor muscles.

## 2. Materials and Methods

### 2.1. Study Design

This study is a randomized, parallel-group, and single blinded clinical trial. The protocol of the clinical trial received approval from the Ethics Committee of the University of Salamanca (ID: 458-2019), and shall be carried out in accordance with the Declaration of Helsinki. The informed consent is available in Spanish and Portuguese with the approved protocol. The clinical trial was registered at ClínicalTrials.gov (NCT04402463), prospectively registered (data 22 May 2020).

The study protocol conforms to the SPIRIT 2013 Statement (Standard Protocol Recommendations for Interventional Trials) [90], and the clinical trial conforms to the CONSORT 2010 Statement (Consolidated Standards of Reporting Trials) [91].

### 2.2. Participants, Recruitment and Sample Size Calculation

A sample of 62 women with CNSNP were recruited between 30 and 65 years old from the community in Guarda, Portugal. Participants were recruited through an online google form, with a questionnaire in Google Docs format, which was disseminated through social network postings (Facebook and Instagram) and the sending of institutional emails from Polytechnic Institute of Guarda to its workers. There were two physiotherapist assessors, who initially assessed participants that responded to the advertisements, and they were different from the physiotherapists who performed the interventions in both groups. In the first visit, the participants provided oral and written forms of all necessary information about the trial, including the study purpose and procedure. After voluntarily signing the informed consent statement, if through a detailed interview they met all inclusion, exclusion, and withdrawal criteria (Table 1), they enrolled into the trial to begin with an initial evaluation with the assessors.

The sample size calculation has been made based on the potential modification of the primary outcomes, neck pain intensity, and neck disability (NPRS and the NDI-PT) from baseline to final assessments. For repeated measurements of the estimated sample size, accepting an alpha risk of 0.05 and a beta risk of 0.2 in a two-sided test, 26 subjects were necessary in the first group and 26 in the second to recognize a statistically significant difference greater than or equal to 2 units (SD = 1.75) (NPRS) or 7 units (SD = 6) (NDI), and to detect small differences in standardized means between groups (Cohen’s d = 0.8), since the intervention with therapeutic exercise is known to have a beneficial effect and we want to assess whether the intervention with GPR has similar or even greater effects. Finally, considering a 15% loss rate during the study, and in order to end up with a sample of 52 subjects, based on the power analysis results, the final sample to be recruited was 62 subjects, 31 in each group. The sample size calculation was made with the software “PASS 15 (NCSS statistical software)” and “The R Project for Statistical Computing”.

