#### 2.6.1. Primary Outcome Variables

The primary measured outcomes of the study will be the change within groups and the differences between groups of the neck pain intensity and the neck disability at the assessment times.

Neck pain intensity

Neck pain intensity will be measured using a numerical pain rating scale (NPRS). This is an 11-point scale ranging from 0, which represents one pain extreme (e.g., “no pain”), to 10, which represents the other pain extreme (e.g., “pain as bad as you can imagine” and “worst pain imaginable”) [95]. The subject is instructed to select the number that best represents the mean of their pain in the last week. Evidence suggests that the perception of pain intensity in subjects with chronic pain must be analyzed by NPRS, and it has been demonstrated to be a valid and reliable scale [96,97]. NPRS has a high test–retest reliability and responsiveness when applied intra-observer reliability of (r = 0.76) in patients with mechanical neck pain [97] and in both literate and illiterate patients with rheumatoid arthritis (r = 0.96 and 0.95) [98]. NPRS also has a high validity with visual analogue scale (VAS) in patients with rheumatic and other chronic pain conditions (pain > 6 months) (correlations range from 0.86 to 0.95) [95], and a high convergent validity with VAS and verbal rating scale (VRS) (r = 0.82–0.92) [99]. Chronic pain patients prefer the NPRS over other measures of pain intensity due to its comprehensibility and ease of completion [99,100].

Neck Disability

We will measure the neck disability associated with pain using the Portuguese version of the neck disability index (NDI–PT), which is valid and reliable with excellent internal consistency (Cronbach’s alpha = 0.95). NDI–PT has a high test–retest reliability with an ICC = 0.91 [101,102], and NDI also has a highly convergent validity with a variety of pain scales (r = 0.40–0.71) [101]. NDI–PT is a patient-completed, condition-specific functional status questionnaire with 10 items including pain, personal care, lifting, reading, headaches, concentration, work, driving, sleeping, and recreation. Each section is rated on a scale of 0 to 5, where 0 means “painless” and 5 means “worst pain imaginable.” The points obtained are added to a total score between 0 and 50. The NDI-PT scores are presented as a percentage of the maximum score, 0–8% without disability; 10–28% mild; 30–48% moderate; 50–64% serious, and 70–100% complete disability [103,104].

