### 2.8. Statistical Analysis

Data were analyzed by using the IBM-SPSS software package (version 23.0). Descriptive data analysis was reported by groups as means ± standard deviation for numeric variables and as frequencies and percentages for categorical variables. In the graphical representation, bar graphs by groups were used for numeric variables, and pie charts were used to represent categorical variables. The main change from baseline to 4 weeks of treatment will be calculated using an intention-to-treat analysis for each outcome measure.

Two-way repeated measures ANOVA were performed. Group factors, as age range, were considered as categorical variables in the statistical model, such as potential covariates, and the Time factor will be used to take into account the two pre-intervention (baseline) and the intermediate and final data in the intervention (2 and 4 weeks of treatment). The interaction between the two factors on the dependent variables was analyzed. When the interaction was statically significant, follow-up tests (post-hoc Sidak test) were performed to determine how the within-participant factors affected the dependent variables, and it could be used as a covariate in the model. The post-hoc Sidak test was calculated to determine which pairs of means have significant differences.

Correlations with Pearson’s r coefficient were determined to analyze whether the values of two or more numeric variables change in conjunction or are related at some time point of the study.

The level of significance for the statistical tests were set at *p* ≤ 0.05 with a confidence interval of 95%.

In order to focus on clinical relevance or clinically worthwhile effects, and assess the magnitude of the change in the result variables, the effect size of both treatments for the group × time repeated-measures ANOVA model were calculated as the partial eta squared (ŋp^2^) when significant, considering 0.01 small, 0.06 medium, and more than 0.14 large effect sizes, and we could use the Cohen d for any pairwise comparisons, when applicable.

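### The sample-size paragraph ties 26 per arm to two different targets without reconciling them, and calls d = 0.8 a small difference when it is a large one

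*Protocol article*

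**What the plan says.** Section 2.2 bases the sample size on the change in the two primary outcomes, neck pain intensity (NPRS) and neck disability (NDI), from baseline to the final assessment. The error rates are "accepting an alpha risk of 0.05 and a beta risk of 0.2 in a two-sided test", and the result is that "26 subjects were necessary in the first group and 26 in the second". That one number is attached to two targets:

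- a "statistically significant difference greater than or equal to 2 units (SD = 1.75) (NPRS) or 7 units (SD = 6) (NDI");
- the aim "to detect small differences in standardized means between groups", with Cohen's d given as 0.8.

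The reason given for the second target is that exercise is known to help, and the authors want to see whether global postural reeducation (GPR) does as well or better. Allowing for 15% loss, 52 becomes 62, or 31 per arm. The paragraph refers to repeated measurements. It gives no correlation between assessments and does not say whether the SDs are of single scores or of change.

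Section 2.8 grades partial eta squared for the group × time model, "considering 0.01 small, 0.06 medium, and more than 0.14 large effect sizes". It mentions Cohen's d for pairwise comparisons without cut-offs. Section 2.6.1 defines the primary outcomes as both change within groups and differences between groups.

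**The concern.** One sample size at one power can match only one standardized difference for a given test. Dividing the printed differences by the printed SDs gives about 1.15, not 0.8, and the article does not explain the gap. The label is a separate problem, because a standardized difference of 0.8 is not small.

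What is at stake is how the primary comparison will be read. Two active exercise programmes are compared, and the paragraph speaks of similar or greater effects. If the trial is said to have 80% power for small differences, a non-significant result invites the conclusion that the two programmes are about equally good. The design cannot support that conclusion.

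**Working it through.** **Inputs (section 2.2).** Two-sided alpha 0.05; power 0.80; 26 per arm; NPRS 2 units, SD 1.75; NDI 7 units, SD 6; d = 0.8; 15% loss. All sample sizes and powers below are for t-tests (noncentral t).

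**1. Reproducing the plan's figure.** With d = 0.8, the two-sample t-test needs 25.5, so 26 per arm. Loss: 52 / (1 − 0.15) = 61.2, so 62, and 26 / 0.85 = 30.6, so 31 per arm. The figures 26, 52 and 62 all follow from d = 0.8.

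**2. The unit differences as between-group differences with the printed SDs.**

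| Target | d | n per arm for 80% power | Power at 26 per arm |
|---|---|---|---|
| NPRS 2 units | 2 / 1.75 = 1.143 | 13.05, so 14 | 98.1% |
| NDI 7 units | 7 / 6 = 1.167 | 12.57, so 13 | 98.5% |
| Stated d | 0.8 | 25.5, so 26 | 80.7% |

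**3. Two readings that reconcile the targets.**

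- *Unit differences are within-group changes.* A paired test at d = 1.143 needs 8.13, so 9 women; at d = 1.167 it needs 7.90, so 8. The between-group target of d = 0.8 is then the stricter one, and 26 per arm covers both.
- *SDs are single-visit SDs and the correlation is zero.* The SD of change is SD × √(2(1 − r)). With r = 0 this is 1.75 × 1.414 = 2.47 and 6 × 1.414 = 8.49. Then d = 2 / 2.47 = 0.81 (25.03, so 26 per arm) and d = 7 / 8.49 = 0.82 (24.07, so 25 per arm). At r = 0.5 the SD of change equals the single-visit SD, and the answers return to 14 and 13.

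**4. Is d = 0.8 small?** For two equal groups, eta squared = d² / (d² + 4) = 0.64 / 4.64 = 0.138. As an observed effect with 26 per arm, t² = 0.64 × 26 / 2 = 8.32 on 50 degrees of freedom, and 8.32 / 58.32 = 0.143. Section 2.8 puts small at 0.01, medium at 0.06 and large above 0.14. For comparison, d = 0.2 gives 0.04 / 4.04 = 0.010 and d = 0.5 gives 0.25 / 4.25 = 0.059.

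**5. Power of 26 per arm for smaller differences.** It is 42.4% at d = 0.5 and 10.9% at d = 0.2. For 80% power at d = 0.2, about 394 per arm would be needed.

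**6. What d = 0.8 means in scale units.** If the printed SDs are those of the analysed quantity: 0.8 × 1.75 = 1.4 NPRS units and 0.8 × 6 = 4.8 NDI units. If they are single-visit SDs with zero correlation: 0.8 × 2.47 = 2.0 and 0.8 × 8.49 = 6.8.

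**The case against.** The strongest reply is that the paragraph never equates 2 / 1.75 with 0.8. It joins two targets with *and*, and calls only the second one between-group. It opens with change from baseline, and section 2.6.1 counts within-group change as part of the primary outcome. On that reading the unit differences are within-group changes, and there is no arithmetic conflict. This stands. A reader might infer that the figures are irreconcilable, or that they agree only under zero correlation, and the article supports neither inference. What remains is that it does not say which reading applies.

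A reader might also reject the zero-correlation route because section 2.6.1 reports test-retest values, such as "intra-observer reliability of (r = 0.76) in patients with mechanical neck pain" and an ICC of 0.91 for the NDI. Those values make zero correlation look unlikely. However, they describe repeat measurement in cited studies, not baseline against four weeks of active treatment, so they do not settle the planning correlation.

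Third, the scale in section 2.8 is for partial eta squared of the group × time term, not for d. The conversion uses a simple two-group contrast and falls on the boundary for large (0.138 to 0.143), not clearly beyond it. That also stands, but it does not rescue *small*.

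Finally, d = 0.8 is printed beside the word, so a statistician can see the true target. Other readers may rely on the word.

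**Conclusion.** The point holds in two parts.

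- **Unexplained targets.** If the unit differences are between-group and the SDs are those of the analysed quantity, they need 14 and 13 per arm and have about 98% power at 26, not the stated 80%. Two other readings remove the conflict, but the article states neither, so this part is an ambiguity to resolve and not a proven error in the number.
- **Wrong label.** This part does not depend on how the unit differences are read. The trial has about 80% power for a large between-group difference, 42% for d = 0.5 and 11% for d = 0.2. A null result cannot exclude small or medium differences between the arms.

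The powers assume a two-sample t-test with 26 analysed per arm and two-sided 0.05. A reader might infer that the trial is too small for its purpose or that 62 was miscalculated. Neither follows: 62 reproduces from d = 0.8, and 26 per arm is at least enough for 2 NPRS or 7 NDI units on each reading worked through here.

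**What to change.** Keep N = 62 and rewrite the paragraph:

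1. Delete *small*. State that 26 analysed per arm give about 80% power (two-sided 0.05) for a large between-group difference, d = 0.8, with about 42% at d = 0.5 and 11% at d = 0.2.
2. Say whether the 2-unit and 7-unit differences are within-group or between-group, and whether the SDs are of a single visit or of change. If they are single-visit SDs and change is analysed, give the assumed correlation.
3. Only then give the between-group difference that d = 0.8 represents: 1.4 NPRS and 4.8 NDI units if the SDs are those of the analysed quantity, or about 2.0 and 6.8 if they are single-visit SDs with zero correlation. Printing either pair before step 2 is settled could put a wrong figure in place of an unclear one.

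The cost is one paragraph, with no change to enrolment, conduct or analysis. The downside is that the sensitivity claim becomes less favourable.

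### The sample-size rationale asks whether GPR is similar to or better than STE, but the plan tests superiority only, has no margin, and calculates its main effect size only after a significant result

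*Protocol article*

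**What the plan says.** The Introduction of the protocol article states the primary objective as a contrast in either direction: "we will evaluate if a global postural exercise method, such as GPR, or a specific therapeutic exercise has a superior effect".

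Section 2.2 sizes the trial by "accepting an alpha risk of 0.05 and a beta risk of 0.2 in a two-sided test" and concludes that "26 subjects were necessary in the first group and 26 in the second", for a "difference greater than or equal to 2 units (SD = 1.75) (NPRS) or 7 units (SD = 6) (NDI") and for a standardized difference of d = 0.8. After allowance for 15% loss, "the final sample to be recruited was 62 subjects, 31 in each group". The same sentence closes by noting that therapeutic exercise already has a known benefit, and adds: "we want to assess whether the intervention with GPR has similar or even greater effects". No margin is attached.

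Section 2.8 plans a two-way repeated measures ANOVA at the 5% level. Sidak follow-up comparisons are run if the interaction is significant. Partial eta squared is calculated "when significant, considering 0.01 small, 0.06 medium, and more than 0.14 large effect sizes". Cohen's d is optional for pairwise comparisons, and a 95% confidence level is mentioned. Group means with SDs, and the intention-to-treat change from baseline to 4 weeks, are planned for each outcome without a significance condition.

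**The concern.** Two parts of the article put different questions. The Introduction asks which treatment is better. Section 2.2 also asks whether GPR is as good as a comparator already taken to work, which is a non-inferiority or equivalence question. Only the first question has a sample size and a test behind it.

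The significance condition in Section 2.8 makes this worse. When the interaction is not significant, the plan calls for neither partial eta squared nor Sidak comparisons. That is the result in which a reader would most need the size of the difference and its uncertainty in order to judge similarity. When the interaction is significant, the effect size shown has been selected for being large.

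Partial eta squared also has no sign and is not in NPRS or NDI units. It cannot show which arm did better, or whether a difference of 2 NPRS points or 7 NDI units has been ruled out, although Section 2.8 offers it as the measure of clinical relevance.

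**Working it through.** **Inputs (Section 2.2).** Two-sided alpha 0.05; power 0.80; d = 0.8; SD 1.75 (NPRS) and 6 (NDI); planning differences 2 and 7; 26 evaluable per arm; 15% loss. The article does not say whether the SDs are of single scores or of changes. They are used here as the SD of whatever is compared between arms at 4 weeks.

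**1. The plan's own figure.**
- n = 2(z₀.₉₇₅ + z₀.₈₀)²/d² = 2 × 7.849/0.64 = 24.5, so 25 per arm. The t-test version gives 25.52, so 26.
- With loss: 26/0.85 = 30.6, so 31 per arm and 62 in total.
- The stated size reproduces as an ordinary superiority calculation at d = 0.8. The raw-unit inputs alone (2/1.75 and 7/6) would need only about 12 to 14 per arm.

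**2. Precision with 26 per arm.** Half-width = t₀.₉₇₅,₅₀ × SD × √(2/26), with t = 2.009 and √(2/26) = 0.2774.
- NPRS: 2.009 × 1.75 × 0.2774 = 0.97 points.
- NDI: 2.009 × 6 × 0.2774 = 3.34 units.
- In SD units: 2.009 × 0.2774 = 0.557.

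The half-width is proportional to the SD. If the relevant SDs were 20% smaller or larger, the range would be 0.78 to 1.17 NPRS points and 2.7 to 4.0 NDI units.

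A result that just misses significance has an estimate of about one half-width, so its interval reaches about two: 1.95 NPRS points or 6.7 NDI units. These are close to the 2 and 7 used for planning.

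**3. How often a real difference gives a null test.** Probability of non-significance = 1 − power of the two-sample t-test with 26 per arm.

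| True difference | Non-significant |
|---|---|
| 0.2 SD | 89% |
| 0.5 SD | 58% |
| 1 NPRS point (0.57 SD) | 48% |
| 3.5 NDI units (0.58 SD) | 46% |

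**4. Selection.** In simulated two-group trials with 26 per arm, the mean estimated d among significant results is 0.77 when the truth is 0.5, and 0.71 when it is 0.3. This uses Cohen's d from a t-test as a stand-in. Partial eta squared from the repeated measures model is subject to the same selection, but these figures do not measure its size there.

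**5. What a claim of similarity would need.** The article gives no margin, so half the planning differences is assumed for illustration. For non-inferiority at one-sided 0.025, 80% power and a true difference of zero, n = 2 × 7.849 × SD²/margin².
- NPRS, margin 1: 2 × 7.849 × 3.0625/1 = 48.1, so 49 per arm, or 116 in total after 15% loss.
- NDI, margin 3.5: 2 × 7.849 × 36/12.25 = 46.1, so 47 per arm, or 112 in total.
- With 26 per arm, power at these margins is about 54% and 56%.

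For equivalence with a 1-point NPRS margin, the whole interval must lie inside ±1. With a half-width of 0.97, the estimate would have to fall within about 0.03 points of zero.

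If the full planning differences (2 and 7) were the margin, non-inferiority power with 26 per arm would be about 98% to 99%. That margin would accept as similar a difference the trial was sized to detect.

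**The case against.** The strongest reply is that the design is coherent and one word is loose. Section 2.2 says that similarity will be assessed, not shown, and says so in a clause of the sample-size rationale. The declared objective is superiority, and both the test and the sample size match it. This stands: a reader might infer that the trial's aim is to demonstrate similarity, and the article does not support that.

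A reader might also infer that all effect sizes are withheld after a null result. That is too broad. Only partial eta squared is literally tied to significance. Group means, SDs and the 4-week change are reported in any case, and Section 2.6.1 defines the primary outcomes to include differences between groups. What remains is that Cohen's d is optional, and that the 95% level mentioned is not tied to the between-group difference.

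Nor does any passage say that a non-significant result will be read as similar. Section 2.9 commits to publishing negative and inconclusive results. The misreading is one that the wording invites, not one that the plan prescribes.

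The arithmetic treats a repeated measures analysis as a single two-group comparison. This is fair as a criticism of the exact figures. It does not alter the conclusion that a null difference test, without a margin, cannot establish similarity.

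Finally, tables of contrasts and intervals are often left to an analysis plan. Their absence alone would not be a finding, but the article itself fixes the significance condition and the wording on similarity.

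**Conclusion.** The point holds as an inconsistency between Section 2.2 and the Introduction, together with a selective reporting rule in Section 2.8. The sample-size arithmetic is not wrong, and the superiority test suits the declared objective. What lacks support is a conclusion of similarity: it has no margin and no decision rule, and a null result is guaranteed no between-group effect size.

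On the assumption that the stated SDs apply to the 4-week comparison, a null result could leave differences of nearly 2 NPRS points or 7 NDI units unexcluded. A true difference of half an SD would be missed more often than found. The present sample is unlikely to support a non-inferiority or equivalence claim at margins well below the planning differences.

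**What to change.** 1. **Section 2.8:** delete the condition that partial eta squared is calculated only on significance. State that the GPR minus STE difference in change from baseline to 4 weeks will be reported with its 95% CI, in NPRS points and NDI units, whatever the p-value of the interaction.
2. **Section 2.2:** replace the clause on similar or greater effects with wording that matches the superiority objective in the Introduction.
3. **Interpretation:** state that a non-significant result will be reported as no difference shown, with the CI used to say which differences remain plausible.
4. **If a similarity claim is still wanted:** fix and justify a margin before unblinding, say whether the claim is non-inferiority or equivalence, and re-check the sample size against it.

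Items 1 to 3 change wording and output only and need no extra patients or data. Their price is that a claim of similarity is given up. Item 4 would probably need a larger trial.
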